### Recruitment {15}

Patients will be recruited from 10 clinical centers most of which are the designated hospitals for patients with severe influenza.

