## Assignment of interventions: allocation

### Sequence generation{16a}, concealment {16b}, and implementation {16c}

According to a stratified block randomization method, all patients are stratified by study center and randomly assigned to the *QZQG* group and placebo group in a 1:1 ratio. The random sequence and the randomization list of every center will be generated by the independent specialist from School of Public Health, Fudan University, China using the PRCO PLAN function of the analysis system of SAS software (SAS, Cary, NC, USA). The randomization sequence will be concealed in a lightproof sealed envelope for emergency unblinding events, which will be kept by the independent specialist and the Sponsor. An independent drug administrator at every center will assign numbered packs of study drugs to eligible patients in order by randomization list.

An emergency letter including the random sequence and assignment has been prepared in all of centers. In any emergency medical situation, such as serious adverse event or deteriorative condition, the unblinding process will be started after contacting the Sponsor and the primary investigator. The investigators from Longhua Hospital Affiliated to Shanghai University of traditional Chinese Medicine will record the details of urgent unblinding and make sure the corresponding patient is excluded. If the rate of drug blinding leakage or emergency letter opening rises more than 20%, this trial will be considered as failure.

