## Statistical methods

### Statistical methods for analyzing primary and secondary outcomes {20a}

The primary study analysis will occur when the last patient has either withdrawn or completed day 28 visit, and will be based on cleaned data for all patients up to and including this point. The clinical data will be managed and analyzed by the independent statisticians from a third party (School of Public Health, Fudan University,) in accordance with the statistical analysis plan. Data management and analysis will use SAS V.9.4 (SAS Institute, Cary, NC, USA).

All statistical inferences will be determined using two-sided tests. *P* < 0.05 will be considered significant, and 95% confidence intervals will be used. Data will be described as the mean, standard deviation, and confidence intervals. If necessary, minimum, maximum, P25, P75, and median values will be provided. Paired measurement data will also show the differences between the mean and standard deviation. When using nonparametric methods, median and mean values will be provided. Count data will be described using the frequency distribution and corresponding proportion. Qualitative information will be described using the positive rate, the number of positive cases, and the denominator.

Baseline data analyses (in FAS and PPS) will include demographic indicators and primary and secondary outcomes before intervention. Measurement data will be described using a *t*-test or *t*’ test (if the variance is absent). Count data will be described using the Pearson’s *χ*^2^ test. Rating data will be described using the two-sample Wilcoxon rank sum test.

Logistic regression model will be used to explore the efficacy (*QZQG* group and placebo group) and factors affecting efficacy. Dependent variable is the proportion of clinical improvement at day 7. In addition to drugs, independent variables also include the basic information and life behavior factors of participants. The basic information includes gender, height, weight, age, and underlying diseases that include chronic obstructive pulmonary disease, asthma, diabetes, hypertension, hyperlipidemia, hyperuricemia, cardiovascular disease, autonomic nervous dysfunction, lung cancer, other tumors, etc. Life behavior factors mainly include smoking and drinking.

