For the efficacy analyses of quantitative variables, comparisons between groups will use repetitive measure analysis of variance and covariance analysis. For qualitative variables, comparisons between groups will use the Pearson’s *χ*^2^ test and center effect analysis will use the Cochran-Mantel-Haenszel (CMH) test. For rating variables, group comparisons will be tested by the Kruskal-Wallis test and the central effect analysis will be tested by the CMH test or grade logistic regression. For center effect analysis, the generalized linear model (GLM) and CMH methods will be used for quantitative and qualitative indicators, respectively. A logistic regression model will be performed for the evaluation and correction of rating variables. For safety analysis, the prevalence of adverse events in the two groups will be compared using the Pearson’s *χ*^2^ test, as well as listing and describing the events that occur during the trial. A description of laboratory test results, electrocardiograph, and chest radiograph will be described as normal/abnormal changes, as well as the relationship between the abnormal changes and the test drug; these changes will be stated.

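### Randomisation is stratified by centre, but the stated group comparison for binary endpoints, including the primary one, is an unstratified Pearson chi-square

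*Protocol article*

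**What the plan says.** In the section on sequence generation, concealment and implementation ({16a} to {16c}), centre is the only stratification factor: "all patients are stratified by study center and randomly assigned" in blocks, 1:1. Recruitment ({15}) gives the number of sites: "Patients will be recruited from 10 clinical centers".

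The section on statistical methods for primary and secondary outcomes ({20a}) sets the treatment comparison for binary data: "For qualitative variables, comparisons between groups will use the Pearson’s" chi-square test. The CMH test gets a different job: "center effect analysis will use the Cochran-Mantel-Haenszel (CMH) test". The same split is stated again further on: "For center effect analysis, the generalized linear model (GLM) and CMH methods will be used for quantitative and qualitative indicators, respectively".

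The primary outcome under Outcomes measurements ({12}) is the proportion of patients improved within 7 days, so it is a qualitative variable in this sense.

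The same section adds a regression on day-7 improvement: "Logistic regression model will be used to explore the efficacy" and the factors that affect it. On its terms: "In addition to drugs, independent variables also include the basic information and life behavior factors of participants". The list names sex, height, weight, age, ten underlying diseases with an open end, smoking and drinking. It names neither centre nor any baseline severity measure.

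**The concern.** Blocking within centre balances the arms inside each centre, so differences between centres largely cancel out of the treatment contrast. The Pearson test does not know this. Its variance is that of all patients pooled and still contains the between-centre spread. If centres differ, the standard error is too large, the true type I error falls below 5%, the interval is wider than the data warrant, and some power is lost.

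Centre differences are plausible here: the sites named under Study setting ({9}) include infectious-disease hospitals and hospitals of traditional Chinese medicine. The protocol gives no figure for their size. What is at stake is precision and a modest amount of power, not a false claim of benefit.

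**Working it through.** **Inputs from the protocol.** Sample size ({14}): placebo 50%, increase of 20 points, 5% level, 90% power, 101 per group, 228 in total. {20a}: all tests two-sided. {15}: ten centres.

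**Inputs assumed.** Between-centre SD of the improvement rate on the logit scale: 0.5, 1.0 or 1.5. Around a 50% control rate, the 10th to 90th percentile of centre rates is then 35% to 65%, 22% to 78% or 13% to 87% (inverse logit of ±1.2816 × SD). Centres of equal size, arms balanced within centre.

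**Step 1, the plan's own figure.** Pooled-variance formula: n = [z_α√(2 × 0.6 × 0.4) + z_β√(0.5 × 0.5 + 0.7 × 0.3)]² / 0.20².
- One-sided: (1.645 × 0.6928 + 1.2816 × 0.6782)² / 0.04 = 100.9, so 101, the stated figure.
- Two-sided: (1.960 × 0.6928 + 1.2816 × 0.6782)² / 0.04 gives 124. With 101 per group, two-sided power is 83.2%.

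The sidedness mismatch is a separate matter. It is noted only because it explains why the powers below start near 83% and not 90%.

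**Step 2, why Pearson is conservative.** With 50% in both arms, Pearson uses variance 0.25 per patient. The variance that drives the within-centre contrast is the mean of p(1 − p) over centres, found by numerical integration: 0.236, 0.207 and 0.177 at SD 0.5, 1.0 and 1.5. In the limit of many centres:
- The standard error is overstated by √(0.25/0.236) = 1.03, √(0.25/0.207) = 1.10 and √(0.25/0.177) = 1.19.
- The effective critical value is 1.96 × 1.03 = 2.02, 1.96 × 1.10 = 2.16 and 1.96 × 1.19 = 2.33, so true type I error is roughly 4.4%, 3.1% and 2.0%.

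With ten centres the effect is slightly weaker, as the simulation shows.

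**Step 3, simulation.** 200 patients, 10 equal centres. Under the alternative, 50% against 70% is held for the trial as a whole, as in {14}.

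| Assumed SD | Pearson type I | CMH type I | Pearson power | CMH power |
|---|---|---|---|---|
| 0.5 | 4.7% | about 5% | 84% | 85% |
| 1.0 | 3.6% | about 5% | 85% | 89% |
| 1.5 | 2.4% | about 5% | 86% | 92% |

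A separate run (202 patients, blocks of 4, 20,000 trials) agrees:
- SD 0.5: type I 4.9% for both tests; power 84.9% (Pearson) and 85.5% (CMH).
- SD 1.0: type I 3.7% and 5.1%; power 85.6% and 88.8%.
- SD 0: power 83.7% and 83.3%, in effect equal; type I 5.6% and 4.8%. The small Pearson excess occurs with no centre effect at all, so it comes from the discreteness of the uncorrected test and not from ignoring centre.
- Seven centres (the number named in {9}) instead of ten changes little: at SD 1.0, power 85.6% and 88.8%.

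**Step 4, the logistic model.** Listed terms: 1 treatment + 4 (sex, height, weight, age) + 10 diseases + 2 (smoking, drinking) = 17. Expected non-improvers: 101 × 0.5 + 101 × 0.3 = 80.8, or 114 × 0.8 = 91.2 with all 228. Per term: 80.8/17 = 4.8 to 91.2/17 = 5.4.

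**The case against.** The strongest reply is that the error is on the safe side and small. Ignoring centre does not create false positives, a centre-stratified CMH test will be run in any case, and at an SD of 0.5 the power gain is about one point. The larger gains need heterogeneity for which the protocol gives no evidence; SD 1.5 is extreme. All of this stands, and it limits the point to an improvement in efficiency.

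Three stronger readings are tempting, and the document does not support them.

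- **A collapse in power.** If 50% against 70% is applied to a typical centre, Pearson power falls to 81%, 71% and 58% across the three SDs, and CMH power to 81%, 76% and 70%. But the overall difference then shrinks to 19.0, 16.9 and 14.6 points, and most of the fall comes from that. {14} states its rates for the trial as a whole, and on that basis Pearson power does not fall.
- **Three competing tests with none chosen.** A reader might infer that the headline result is open to choice. {20a} gives each method a role: Pearson for group comparison, CMH for centre effects, logistic regression for exploration. Further detail may properly sit in the analysis plan, which is not shown.
- **An overfitted model undermining the result.** About five non-improvers per term is thin, but the model is described as exploratory and does not drive the primary test.

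**Conclusion.** The point holds as a modest, nearly free improvement. The stated comparison for the primary endpoint ignores the only factor used to stratify randomisation. If centres differ, the test is conservative (about 4.7%, 3.6% or 2.4% instead of 5%), the interval is too wide, and about 1 to 6 points of power are given up. If they do not differ, the two tests have practically equal power, so stratifying costs nothing material.

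The sizes rest on assumed between-centre SDs, equal centres and balanced allocation within centre. The direction needs only that centres differ and that arms are balanced within them. As a secondary matter, the exploratory model would say more about the treatment effect if it included centre and baseline severity; its 17 listed terms leave the primary test untouched.

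**What to change.** In {20a}, before unblinding:

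1. Name the centre-stratified CMH test, reported with the Mantel-Haenszel risk difference and its 95% CI, as the primary between-group comparison for the primary endpoint.
2. Fix a rule for pooling very small centres, since a centre with patients in only one arm, or with the same outcome in every patient, adds nothing to the CMH statistic.
3. Keep the Pearson chi-square as a sensitivity analysis.
4. Add centre, baseline ordinal category and baseline NEWS2 to the exploratory logistic model.

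The cost is wording. CMH is already planned and centre is known at randomisation. {20a} already foresees a baseline description of the primary outcome measures, so the severity terms should need no new visits. No extra patients are required.

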### Methods for any additional analyses {20b}

Subgroup analysis of all endpoints will be conducted based on chronic respiratory diseases (with or without), complications (with or without) and course of disease (< 3 days and ≥ 3 days). Subgroup analyses will be produced where appropriate and where the number of patients in each subgroup is sufficient.

### Definition of analysis population relating to protocol nonadherence {20c}

The intent-to-treat (ITT) population is defined as all randomized patients, whether or not the patient received the assigned treatment. The ITT patients will be analyzed according to the treatment assigned at randomization. The ITT population includes the patients who agree to enroll in the study and sign an informed consent form. However, ITT population involves those who have never received study drugs or never completed observation records. Efficacy analyses will be conducted for the modified intent-to-treat (mITT) population. This is defined as all patients randomized who received at least one dose of *QZQG* formula and were centrally assessed as RT-PCR positive for influenza at any timepoint, with patients grouped according to the treatment assigned at randomization. The per-protocol set is used to analyze the main outcome for evaluating efficacy and to examine the consistency of the results from the mITT. The PPS is defined as follows: (1) full compliance with inclusion and exclusion criteria; (2) the compliance of medication consumption is over 80%; (3) the patients complete the test and record of the outcome and safety evaluation at every time node; and (4) completion of the clinical trial without major protocol violation. The safety analysis set (SAS) is defined as patients who received any amount of study treatment. Patients will be analyzed according to the treatment received. Patients who were randomized to the study but who did not receive any study drug will not be included in the safety population. The SAS will be used for the analysis of all safety indicators. Multiple imputation will be used for missing data.

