#### Inclusion criteria

*The inclusion criteria are as follows:*
Diagnosis of influenza A and/or B by a positive Rapid Influenza Diagnostic Test (RIDT) or reverse transcriptase-polymerase chain reaction (RT-PCR).• Positive results from local tests are acceptable if conducted within the 24 h prior to screening.• A patient with a negative RIDT may be enrolled if influenza is suspected based on local surveillance data or if the patient reports contact with a known case of influenza within the prior 7 days and all other inclusion criteria are met.Granting of written informed consent.Male or female aged 18 to 65 years at the time of signing informed consent form.Ability to comply with the study protocol, in the investigator’s judgment.Participants who require hospitalization for severe influenza or acquire influenza during hospitalization, the severity of which requires an extension of hospitalization.Participants will require at least one of the following objective criteria of severe influenza: (i) duration with axillary temperature over 39 °C ≥ 3 days, accompanied by severe cough, sputum, blood sputum, or chest pain; (ii) rapid respiratory rate (≥30 times per minute), difficulty breathing and cyanosis of lips; (iii) arterial oxygen saturation (SaO2)/ pulse oxygen saturation (SPO2) ≤94% in room air condition; (iv) requires ventilation or supplemental oxygen to support respiration; (v) with only one complication related to influenza (e.g., pneumonia, central nervous system involvement, myositis, rhabdomyolysis, acute exacerbation of chronic kidney disease, asthma or chronic obstructive pulmonary disease (COPD), severe dehydration, myocarditis, pericarditis, exacerbation of ischemic heart disease).The time interval between the onset of symptoms and randomization is within 96 h. The onset of symptoms is defined as either time of the first increase in body temperature (≥ 38 °C) or time when the patient experiences at least one general or respiratory symptom.Conforming to the standard of TCM syndrome differentiation.

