#### Intervention description {11a}

*The intervention is described as follows for the experimental and control groups:*

The *QZQG* group will receive two bags of *QZQG* formula granules (4.6 g/per bag), twice a day, 30 min after eating for 7 days. Whole ingredients of *QZQG* formula include *Rhizoma seu Radix Notopterygii* (*Qiang Huo*) 18g, *Gypsum Fibrosum* (*Sheng Shi Gao*) 25g, *Codonopsis Radix* (*Dang Shen*) 7.5g, *Angelicae Dahuricae Radix* (*Bai Zhi*) 18g, *Saposhnikovia Divaricata* (*Fang Feng*) 18g, *Rhizoma Atractylodis* (*Fu Chao Cang Zhu*) 18g, *Pinellia Ternata* (*Ban Xia*) 9g, *Taraxacum* (*Pu Gong Ying*) 15g, *Astragalus Membranaceus* (*Huang Qi*) 15g, *Lophatherum Gracile *(*Dan Zhu Ye*) 3g, *Radix Ophiopogonis* (*Mai Dong*) 15g, *Rehmannia Glutinosa* (*Sheng Di Huang*) 12g, *Scutellaria baicalensis* (*Huang Qin*) 12g, *Asari Radix Rhizoma* (*Xi Xin*) 3 g, *Ligusticum wallichii* (*Chuan Xiong*) 12g, *Honey-fried Herba Ephedrae*(*Zhi Ma Huang*) 6g, *Vitex negundo*(*Huang Jing Zi*) 20g and *Clycyrrhizae Radix Et Rhizoma* (*Gan Cao*) 12g. *QZQG* formula granules and placebo granules are manufactured and provided by Sichuan New Green Pharmaceutical Technology Development Co., Ltd. The Chinese herbal medicine placebo with the same weight as the test drugs consists of 20-fold dilution of 4.60 g of *QZQG* formula granules and maltodextrin with the addition of artificial pigment and flavoring agents.

The placebo group will receive placebo granules and used the same medication as the test group. Placebo is identical to the test drug in appearance, smell, and taste. This preparation of placebo has been frequently used in herbal medicine trials in China. All drugs are hidden in a uniform package with the same label, and each package contains a 7-day dose. Both test drugs and placebo will be packaged and labeled by School of Public Health, Fudan University, according to the random number table and drug blinds.

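### The mITT definition requires a dose of QZQG, which read literally excludes every placebo patient, and sets no baseline limit on the PCR result that decides entry

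*Protocol article*

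**What the plan says.** The protocol article, section Definition of analysis population {20c}, assigns the efficacy work to one set: "Efficacy analyses will be conducted for the modified intent-to-treat (mITT) population". It defines that set as "all patients randomized who received at least one dose of *QZQG* formula and were centrally assessed as RT-PCR positive for influenza at any timepoint", and the sentence continues "with patients grouped according to the treatment assigned at randomization".

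Intervention description {11a} states what controls take: "The placebo group will receive placebo granules and used the same medication as the test group". The safety set, defined later in {20c}, is worded neutrally between the arms: "The safety analysis set (SAS) is defined as patients who received any amount of study treatment".

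On confirmation of infection, the Inclusion criteria accept a positive local rapid test or RT-PCR, and add an exception: "A patient with a negative RIDT may be enrolled if influenza is suspected based on local surveillance data". The exception also covers recent contact with a known case. A positive central PCR is therefore not a condition of entry.

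**The concern.** There are two separate faults in one definition.

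**Dose condition.** A rule that asks for a dose of the experimental product cannot be met by a correctly treated control. Applied word for word by a programmer, it leaves the efficacy analyses without a comparison group.

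**PCR condition.** This one survives a charitable reading of the first. With no limit on when the positive sample was taken, a result obtained after dosing can decide whether a patient is analysed. Background and rationale {6a} argues that herbal extracts act against influenza virus. If the study drug does so, it could change who turns positive later, and so who is counted in each arm. The comparison would then be restricted by something treatment may have altered, and randomization would not fully protect it. Blinding does not remove that kind of selection.

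**Working it through.** The plan gives no figure for the size of the mITT, so there is none to reproduce. The check is a reading of the rule against the rest of the article, with simple arithmetic for scale.

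**Inputs.** Total planned enrolment is 228 (Sample size {14}). Allocation is 1:1 (Sequence generation {16a}), so 228 / 2 = 114 per arm. The share of patients without a positive baseline central PCR is not in the documents; 5–10% is assumed here.

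**Step 1: the dose condition taken literally.**
- QZQG arm: up to 114 patients can meet it.
- Placebo arm: 0 of 114 can meet it if dosed as allocated.
- The set is nevertheless to be grouped by assigned treatment, and Statistical methods {20a} compares the QZQG group with the placebo group. The definition and its use cannot both stand.
- The placebo "consists of 20-fold dilution of 4.60 g of *QZQG* formula granules and maltodextrin", so one could argue that controls do receive some QZQG. The article calls the product placebo throughout and keeps the formula's name for the test drug, so this does not rescue the wording.

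**Step 2: who is affected by the open timing of the PCR result.** This compares the article's rule with one tied to a sample taken at or before the first dose, for patients who meet the dose condition.

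| Central PCR at baseline | Central PCR later | Article's rule | Baseline rule |
|---|---|---|---|
| Positive | Any | In | In |
| Not positive | Positive | In | Out |
| Not positive | Never positive | Out | Out |

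Only the middle row changes status. Such patients are possible because entry can rest on a local test, or on clinical suspicion after a negative rapid test.

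**Step 3: scale.** Let b be the share without a positive baseline central sample and c the share of those who turn positive later. The number whose status depends on a post-dose sample is 228 × b × c, which is at most 228 × b.
- b = 5%: 228 × 0.05 = 11.4, about 11 patients.
- b = 10%: 228 × 0.10 = 22.8, about 23 patients.

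These are ceilings, reached only if c = 1. The documents give no value for c.

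**The case against.** **The dose condition is a drafting slip.** This is right. Grouping by assigned treatment, the two-group comparisons in {20a} and the sample size in {14} all presuppose a control arm. A reader might infer that the trial would really be analysed without its placebo patients; the rest of the article excludes that, so 0 of 114 describes the wording and not an expected loss. What remains is that a defining sentence for the efficacy population is wrong as written.

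**The PCR condition is not confined to samples after randomization.** Also right. A positive baseline sample qualifies, so membership depends only partly on later data.

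**Post-dose sampling and its sensitivity to treatment are not shown.** Plans for assessment {18a} sends swabs to a central laboratory without giving times, and the timeline in Table 2 has no PCR row. The argument in {6a} concerns herbal medicines in general and does not show that QZQG changes PCR detection. This limits how large the problem can be said to be. It does not close the gap, because the definition itself admits a result from any time.

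**An ITT analysis may be planned elsewhere.** A reader might infer that no ITT result is intended, since {20c} defines the set without naming an endpoint for it. That cannot be established: the article says ITT patients are analysed as assigned, and the statistical analysis plan is not shown.

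**The FAS label.** Statistical methods {20a} says "Baseline data analyses (in FAS and PPS) will include demographic indicators", and FAS is expanded only in the abbreviations. It is used there for baseline description, does not touch the primary comparison, and could mean the ITT set as easily as the mITT. Nothing is concluded from it.

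**Conclusion.** The mITT definition needs correcting in two places. The dose condition contradicts the design, with certainty and without any assumption; its intent is clear and the repair is one phrase. The PCR condition is a real weakness of the rule, because it lets post-dose samples settle membership for patients without a positive baseline central sample.

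The extent of the second fault is not known from the documents. At most 11–23 of 228 patients would be affected under the assumed 5–10%. Reading that range as the expected number would overstate it, since patients who are never positive are excluded under either rule. Any bias also depends on treatment changing later PCR results, which the article's rationale makes plausible but does not demonstrate for QZQG.

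**What to change.** Redefine the mITT as all randomized patients who received at least one dose of their assigned study drug (QZQG or placebo) and were centrally RT-PCR positive on the sample taken at or before the first dose, analysed by the arm assigned at randomization. Settle this before unblinding.

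It is also advisable to state a supporting analysis of the primary endpoint in the ITT set, which {20c} already defines, unless the statistical analysis plan contains one.

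The cost is a change of wording and, if not already planned, one further table. A few patients who are positive only on later samples leave the mITT; they remain in the ITT set.

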	Adverse events are definitely caused by the disease or the main cause of the disease

Participants may experience exacerbations due to natural disease progression, poor drug efficacy, or other reasons, including but not limited to respiratory failure, acute necrotizing encephalopathy, shock, multiple organ dysfunction, and other conditions that require clinical monitoring. If the participant is judged to be critically ill in the process of trial, the research doctor at the center where the participant is located should report to the sponsor and the ethics committee within 24 h. The trial drug intervention should be stopped at the same time. The research doctor should immediately initiate a clinical treatment regimen on severe clinical situation. When necessary, the sponsoring unit and the project funding department will organize multidisciplinary consultations and propose a comprehensive clinical treatment plan. The branch center and the sponsor are jointly responsible for the treatment, follow-up monitoring, and follow-up of critically ill participants.

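### The supportive per-protocol analysis of the day-7 outcome drops patients who die before day 28, and those whose drug is stopped early for critical illness if all 14 doses are counted, so it selects on outcome

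*Protocol article*

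**What the plan says.** All references are to the protocol article.

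- **Role of the sets ({20c}).** "Efficacy analyses will be conducted for the modified intent-to-treat (mITT) population". The mITT needs at least one dose and central RT-PCR positivity; it has no completeness or compliance condition. For the other set: "The per-protocol set is used to analyze the main outcome for evaluating efficacy and to examine the consistency of the results from the mITT".
- **PPS conditions ({20c}).** Besides meeting the entry criteria, a patient qualifies only if (2) "the compliance of medication consumption is over 80" per cent, (3) "the patients complete the test and record of the outcome and safety evaluation at every time node", and (4) there is "completion of the clinical trial without major protocol violation". No exception is written for death or for a drug stop that the protocol itself requires.
- **Visits (Table 2).** Efficacy and safety assessments run from day 0 to day 28.
- **Primary outcome ({12}).** Clinical improvement within 7 days, met by either of two criteria. Death is category 7 of the ordinal scale.
- **Drug stop (Assessment of adverse events).** "If the participant is judged to be critically ill in the process of trial", the event is reported, and "The trial drug intervention should be stopped at the same time". Section {11b} also halts or modifies study drug for hypoxemia, low blood pressure and confusion, among other signs.
- **Dosing ({11a}).** Twice a day for 7 days.

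**The concern.** A per-protocol set is meant to remove patients who did not follow the plan. These conditions also remove patients because of how their illness went. Death is a value on the primary scale, so it is an observed result and not missing data; yet a patient who dies cannot attend the later visits and so leaves the set. A patient whose drug is stopped because the protocol requires it may then fail the dosing rule for having followed the protocol.

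At stake is the second of the PPS's two stated purposes. If membership depends on outcome, agreement or disagreement between the PPS and the mITT may come from the set definition and not from adherence. Multiple imputation does not help, because these patients are outside the set by definition.

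**Working it through.** The plan states no figure on this point, so there is none to reproduce. The design rates are used as inputs.

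**1. Who leaves through conditions (3) and (4).** Table 2 has visits at days 14, 21 and 28. A patient who dies before the day-28 visit lacks at least one node and has not completed the trial, even with full dosing and a known day-7 outcome.

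**2. Who leaves through condition (2).** From {11a}: 2 administrations × 7 days = 14.

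- 11/14 = 78.6%, fails
- 12/14 = 85.7%, passes

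If all 14 planned administrations are the denominator, a drug stop for critical illness before the 12th (the second on day 6) fails the rule. A later stop passes, and critical illness after day 7 does not touch dosing. The article does not say which denominator applies.

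**3. Effect on an arm's rate.** Let p be the true improvement rate, f the share removed, and q the share of removed patients who had improved within 7 days. The PPS rate is (p − f·q)/(1 − f). With q = 0 it is p/(1 − f), the highest value that the arm's rate can take for that f. With q = p it does not change.

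Inputs: placebo 50% and a 20-point increase, hence 70% for QZQG (Sample size {14}). The documents give no rate of death or critical illness by arm in this trial, so f = 5% and 10% are assumptions. With q = 0:

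- 0.50/0.95 = 52.6%; 0.50/0.90 = 55.6%
- 0.70/0.95 = 73.7%; 0.70/0.90 = 77.8%

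| Removed, placebo / QZQG | True rates | PPS rates | PPS difference (points) |
|---|---|---|---|
| 5% / 5% | 50% / 70% | 52.6% / 73.7% | 21.1 |
| 10% / 10% | 50% / 70% | 55.6% / 77.8% | 22.2 |
| 10% / 5% | 50% / 70% | 55.6% / 73.7% | 18.1 |
| 5% / 10% | 50% / 70% | 52.6% / 77.8% | 25.1 |
| 10% / 5% | 50% / 50% | 55.6% / 52.6% | −2.9 |
| 5% / 10% | 50% / 50% | 52.6% / 55.6% | +2.9 |

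Differences are taken before rounding.

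**4. Which arm rises more.** The rise with q = 0 is p·f/(1 − f), which depends on p as well as f. With 6% of placebo and 5% of QZQG removed:

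- placebo: 0.50 × 0.06/0.94 = 3.2 points
- QZQG: 0.70 × 0.05/0.95 = 3.7 points

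The arm with fewer removals rises more here, so no general direction follows.

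**The case against.** **The main result does not depend on the PPS.** This stands. Efficacy analyses are assigned to the mITT, which keeps these patients whatever their dosing or visit record. A reader might infer that the trial's efficacy conclusion is biased; the article does not support that, and no success rule in it rests on the PPS.

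**Such conditions are ordinary, and details belong to the SAP or the blind review.** This stands in part. Over 80% compliance and no major violation are usual, and the compliance denominator may well be set elsewhere. But the demand for every record and for trial completion is stated here without exception, for an outcome read by day 7. That is a rule as written, not a detail left open.

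**Not every critically ill patient is removed.** This stands. The adverse event section stops the drug but provides for continued follow-up of critically ill participants. Someone whose drug is stopped after the 12th administration, or who becomes critical after day 7, can stay in the set if all visits are recorded and the trial is completed.

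**Not every removed patient is a failure.** This also stands. A patient who met a criterion on day 4 and died on day 20 is an improver under {12}, and removing that patient lowers the PPS rate. The table in the working assumes that there are no such patients.

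**The removal rates are unsupported.** They are assumptions. The Background cites ICU admission in 5–10% of hospitalised influenza patients, but this trial excludes patients already critically ill, so that figure does not transfer directly.

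**Conclusion.** The point holds as a defect of the supportive analysis. As written, deaths before day 28 leave the PPS with certainty. Patients whose drug is stopped for critical illness before the 12th of 14 administrations leave if compliance is counted against all planned doses. Those who deteriorate in the first week are mostly primary-outcome failures, so the set selects partly on the outcome it analyses.

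At the design rates, removing 5–10% raises an arm's PPS rate by at most 2.6 to 7.8 points, and the 20-point difference becomes 18.1 to 25.1 in the cases shown. With no true difference, unequal removal of 5% and 10% creates a shift of about 2.9 points in either direction. These sizes rest on assumed removal rates and on no removed patient having improved. That second assumption makes each arm's rise an upper bound; the differences are illustrations.

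A reader might also infer that the PPS is always tilted against QZQG, or that the rate rises most in the arm with more failures. Neither follows: the direction depends on the removal share and the improvement rate in each arm. The importance is minor, because the mITT result is untouched.

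**What to change.** Reword the PPS definition before database lock:

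- Limit conditions (3) and (4) to the records and conduct needed for the day-7 primary outcome.
- Count the 80% rule against doses due up to death or a protocol-required drug stop.
- Keep these patients in the PPS and classify them by the primary outcome definition in {12}. Those who die or become critically ill by day 7 without having met the improvement criteria count as not improved. Those who met the criteria within 7 days and deteriorated later remain improvers.

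The cost is wording in the protocol or SAP. The downside is that the PPS keeps some patients with short exposure. No change to any dose or stopping rule is proposed.
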